### Psychological study

Volunteer patients will attend 3 individual interviews with the psychologist. The interviews will take place at key-moments of the procedure that are likely to trigger a significant emotional response: (1) within a month following the inclusion, (2) after the results of the first screening round, and (3) one year after the first screening round. The psychological study relies on the principles of the grounded theory approach [25]. It is inductive and iterative. The patient-physician communication will be quantitatively and qualitatively analyzed.

Individual interviews will be conducted with each of the volunteers. The psychologist has an active-listening role, asking clarification questions while enabling the patient to address other topics of his choice. Data collection will continue until theoretical saturation is achieved [26]. The psychological interviews will be qualitatively analyzed by two independent psychologists. Each psychologist will identify key points of the data (codes) within several levels of themes (categories). Data will be entered in N’Vivo software to facilitate the in-depth analysis of the material. Connections within and between categories will be identified until a meaningful theory is generated [27].

## Discussion

The originality of this study in a PAD / AAA population is to involve together, for the screening of cancer in high risk patients, clinicians, radiologists, pathologists as well as psychologists.

Lung cancer is the leading cause of cancer-related death worldwide [28]. This tumor is diagnosed in most cases at an advanced stage with prevalent distant metastases and reduced survival. By considering CTCs detection in a very high-risk selected population for tobacco-induced cancer, we expect to reduce false positive results of conventional imaging and to detect earlier pulmonary but also extra-pulmonary, malignancies when they are still curable.

Smoking cessation is an important factor in reducing mortality. In the NLST study, a cessation of smoking for at least 15 years associated with LDCT screening resulted in a 38% reduction in mortality, much higher than that achieved by the single effect of CT [29]. Participation in a screening study therefore presupposes for active smokers the parallel commitment in a smoking cessation procedure.

Cancer screening procedures have been associated to psychological adverse effects, particularly consequently to false positive results, over-diagnosis and over-treatment. Lung cancer screening causes an increase in anxiety [30], raising concerns about the short and long-term effects of screening on the psychological well-being of patients. By assessing the emotional and psychological impact of screening for cancers due to tobacco, we expect to identify 1/ specific fear, anxiety and psychological distress mechanisms, 2/ coping strategies that may benefit other patients, 3/ stress factors specifically linked to the screening procedure and/or to the medical information delivered to patients. By assessing the patient-doctor communication strategies, we expect to adjust and improve health professional communication skills respectful of patient psychological well-being.

Repetition of screening examinations raises the question of the risks associated with low-dose but repeated diagnostic irradiations. Irradiation delivered by a LDCT or a PET scanner is not negligible (1.5 mSv for LDCT) and may cause an excess risk of cancer. However, this risk appears much lower than the number of spontaneous cancers observed in a population at risk, which justifies the completion of these examinations [31]. In the NLST study, a positive examination was defined by the presence of at least one non-calcified nodule larger than or equal to 4 mm which led to a 27% positive test rate, 96% of which were false positives. We chose to apply the criteria of the NELSON study which demonstrated a significant reduction of false positive rate.

Common risk factors and pathophysiological processes have been highlighted in cancer and atherosclerosis, involving genetic alterations, inflammatory pathways, uncontrolled cell proliferation and pro-thrombotic processes [32]. Secondary cardiovascular prevention measures help delay vascular related events in PAD patients whereas epidemiological data underline an increase incidence in cancer and related death in the follow-up, compared with the general population, particularly for tobacco-related cancers [33, 34]. Large data from population-based cohort studies highlighted a 40% increased risk for cancer among patients with intermittent claudication [34, 35]. Prospective data reported a prevalence of 11.5% for malignancies in patients with critical leg ischemia and half of this population had died within 6 months [8]. However, not all of the patients with critical leg ischemia were investigated for occult malignancy, but only those with suggestive symptoms. The true prevalence of occult cancer in this population could thus be higher. The clinical benefit of a special workup for neoplasms in patients with PAD and a history of cigarette smoking has never been investigated. Furthermore, most patients diagnosed with cancer in the follow-up after PAD treatment exhibited advanced stage and poor survival [11, 34]. The clinical benefit of early cancer detection in this population may thus be expected. Although the lung is particularly susceptible for tobacco-induced cancer, a screening strategy should also have the potential to detect early stage neoplasm in all target organs. Circulating tumor cell search in the peripheral blood may represent a reliable tool suggestive for occult cancer in high risk PAD patients [18].

Different CTC isolation/detection methods exist. Transition of epithelial differentiation to mesenchymal phenotype is an important biological process leading to the generation of more aggressive sub-populations of CTCs. These invasive CTCs may not be captured with isolation/detection methods considering epithelial-lineage or tissue markers leading to false negative results, especially in patients with lung cancer [36]. The DETECTOR study will be the first prospective study analyzing the interest of CTC search with ISET technique in association with LDCT, possibly supplemented by whole-body imaging, in the screening strategy of smoking-associated cancers in PAD patients. A main challenge of the study is the detection method of CTCs, considering their low abundance in peripheral blood, fragility, heterogeneity and the lack of organ-specific markers [37]. If positive this study could pave the way for other cardiovascular population with a history of smoking, such as patients with coronary artery disease.

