### Management of incidental findings

First-line screening incidental findings and adapted screening strategy are displayed in Table 2. In case of negative LDCT or incidental lung nodule(s) with a volume < 50 mm^3^ and absence of CTCs, this screening strategy will be repeated once a year for a total of 3 consecutive rounds. Participants will be excluded from further screening when diagnosed with lung cancer or extra-pulmonary malignancy. In case of incidental lung nodule(s) with a volume > 500 mm^3^, in the presence or absence of CTCs, a specific multidisciplinary team meeting will discuss diagnostic and pre-therapeutic evaluation for lung cancer [23]. In case of incidental lung nodule(s) with a volume between 50 and 500 mm^3^ and presence of CTCs, diagnostic and pre-therapeutic evaluation for lung cancer will also be performed. In the absence of CTCs, volume doubling time - evaluated through a second LDCT performed three months later - will be taken into consideration for adapted diagnostic management. In case of negative LDCT or incidental lung nodule(s) with a volume < 50 mm^3^, and presence of CTCs, a contrast enhanced whole-body scanner and PET/CT associated with clinical head and neck examination and cytological examination of the urine will be performed for extra-pulmonary malignancy screening and management (Fig. 1).

**Table 2 Tab2:** First-line screening incidental findings and adapted screening strategy

Low –dose chest CT and search for CTCs	No incidental lung nodule or nodule(s) <50mm^3^	Incidental lung nodule(s) with volume between 50 and 500mm^3^	Nodule(s) >500mm^3^
No CTC	Next screening round at one year	Measure of volume doubling time at low-dose chest CT 3 months later	Diagnostic and pretherapeutic evaluation
Presence of CTC	Contrast enhanced whole-body scanner and PET/CT examination of the head and neck cytological examination of the urine	Diagnostic and pretherapeutic evaluation	Diagnostic and pretherapeutic evaluation

*CTC: circulating tumor cells; PET/CT: Positron emission tomography-computed tomography*

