### Statistical analysis and sample size

Data will be analyzed using SAS and R software. Alpha level for statistical significance (p) will be set at less than 5%. Characteristics of the study population will be described as mean plus or minus standard deviation for continuous variables with a normal distribution and as median [interquartile range] for skewness distribution. Categorical variables will be described as numbers and proportions. Student’s t-test or nonparametric Wilcoxon test will be used to compare quantitative parameters between different groups of patients and Chi2 test or Fischer test for qualitative parameters.

The primary outcome will focus on the sensibility and specificity of the screening strategy associating detection of CTCs and LDCT. Statistical analysis is in accordance with the STARD (Standards for Reporting of Diagnostic Accuracy Studies) guidelines [24]. To meet the primary objective, sensitivity will be estimated by dividing the number of patients diagnosed by the CTC method by the number of patients with lung cancer confirmed by the reference technique, i.e. LDCT. The results will be expressed with a binomial proportion 95% confidence interval. Specificity will be estimated by dividing the number of patients diagnosed with CTC as cancer-free with the number of patients without lung cancer. Secondary evaluation criteria will be analyzed using the same statistical methods as those used for the primary endpoint.

Assuming 10% prevalence of smoking-associated cancer in the studied population [8], if we aim to study a total of at least 30 detected cancers, including baseline and repeat screening rounds, we need to enroll a total of at least 300 participants.

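### Under the Table 2 rule CTC can only escalate management, so adding it cannot reduce false-positive work-ups relative to LDCT alone, and the stated estimators cannot show what it adds

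*Protocol article*

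**What the plan says.** The protocol article's Discussion gives one expected benefit of CTC detection as follows: "we expect to reduce false positive results of conventional imaging".

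The section Management of incidental findings, with Table 2, fixes how CTC acts in each nodule category:

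- **No nodule, or below 50 mm³.** Without CTC, the participant waits for the next yearly round. With CTC, "a contrast enhanced whole-body scanner and PET/CT associated with clinical head and neck examination and cytological examination of the urine will be performed".
- **50 to 500 mm³.** "In the absence of CTCs, volume doubling time - evaluated through a second LDCT performed three months later - will be taken into consideration"; the table entry reads "Measure of volume doubling time at low-dose chest CT 3 months later". With "presence of CTCs, diagnostic and pre-therapeutic evaluation for lung cancer will also be performed".
- **Above 500 mm³.** "in the presence or absence of CTCs, a specific multidisciplinary team meeting will discuss diagnostic and pre-therapeutic evaluation for lung cancer".

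On the imaging criteria, the Discussion adds: "We chose to apply the criteria of the NELSON study which demonstrated a significant reduction of false positive rate". The Background describes that study's protocol as resting on nodule volume and growth rate.

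Under Objectives, the primary aim is the diagnostic value of LDCT and CTC taken together. Statistical analysis and sample size repeats this as the primary outcome. Its formulas differ: sensitivity is the number of patients detected by CTC over lung cancers confirmed by LDCT as the reference technique, and specificity is the number of CTC-negative patients over patients without lung cancer.

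**The concern.** The expected benefit and the rule point in opposite directions. To lower false positives of imaging, a second test must be able to stop some work-ups that imaging would start. In Table 2 the second test can only start or bring forward work-ups.

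This matters because the Background names false positives leading to repeated and invasive procedures as a main harm of screening, and the Discussion ties them to psychological harm. The stated rationale therefore points the wrong way on a harm the article itself stresses.

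The useful question is how many extra cancers CTC finds for each extra false-positive work-up. Every participant is scheduled for both tests, so the data can largely answer it. The stated estimators cannot.

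**Working it through.** **1. The plan's own figure.** Target cancers divided by prevalence: 30 / 0.10 = 300 participants, as stated. That leaves 300 − 30 = 270 without cancer. The enrolment arithmetic is not in question.

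**2. Table 2 as an ordered rule** (0 = next yearly round, 1 = repeat LDCT at three months, 2 = work-up):

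| Nodule category | CTC absent | CTC present | Effect of CTC |
|---|---|---|---|
| None or < 50 mm³ | 0 | 2 | escalates |
| 50–500 mm³ | 1 | 2 | escalates |
| > 500 mm³ | 2 | 2 | none |

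CTC escalates in 2 of 3 categories and de-escalates in 0 of 3. The CTC-absent column uses only volume and growth, so it serves as LDCT alone under the criteria the article says it adopted. Everyone worked up under LDCT alone is also worked up under the couple. Specificity for work-up is therefore at most that of LDCT alone. This step needs no assumed figure and no independence between the tests.

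**3. Size of the rise.** Among cancer-free participants let a, b, c be the shares in the three nodule categories, v the share of 50–500 mm³ nodules worked up on growth, and q the CTC false-positive rate (taken as the same in every category and unrelated to growth).

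- LDCT alone: bv + c
- Couple: aq + b[q + (1 − q)v] + c
- Difference: q[a + b(1 − v)], which is zero when q = 0 and positive otherwise

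None of a, b, c, v or q is in the article. With assumed values, 270 cancer-free participants and one round:

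| a / b / c | v | LDCT alone | Added, q = 1% | q = 5% | q = 10% |
|---|---|---|---|---|---|
| 80 / 18 / 2% | 5% | 7.8 | 2.6 | 13.1 | 26.2 |
| 80 / 18 / 2% | 20% | 15.1 | 2.5 | 12.7 | 25.5 |
| 70 / 27 / 3% | 5% | 11.7 | 2.6 | 12.9 | 25.8 |
| 70 / 27 / 3% | 20% | 22.7 | 2.5 | 12.4 | 24.7 |

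First row at q = 5%: 270 × 0.05 × (0.80 + 0.18 × 0.95) = 13.1.

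**4. A cruder comparator.** If every nodule of 50 mm³ or more were worked up at once, there would be 270 × 0.20 = 54 or 270 × 0.30 = 81 false-positive work-ups. The couple gives fewer than that in every row above, but so does LDCT alone, by a wider margin whenever q > 0. The saving comes from the growth check, not from CTC.

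**5. What the stated estimators can show.** If LDCT defines the lung cancers, LDCT detects all of them, and its sensitivity is 100% by construction. A lung cancer found only through CTC has no place in the denominator. An extra-pulmonary cancer found through CTC is also outside it. Read literally, that patient belongs to those without lung cancer and counts against CTC specificity.

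**6. Precision of the missing contrast.** Because the couple can only add positives, discordant pairs run one way. An exact two-sided McNemar test at 5% needs at least 6 of them: 2 × 0.5⁶ = 0.031, against 2 × 0.5⁵ = 0.0625 for five. With 30 cancers, the chance of 6 or more is 7% for a true sensitivity gain of 10 points, 57% for 20, 80% for 25 and 92% for 30.

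**The case against.** **The comparator is inferred.** The article never writes out an LDCT-alone rule, and the Discussion speaks only of conventional imaging. The false-positive figures it quotes come from a US trial with a cruder definition of a positive scan (27% positive, 96% of these false). Against that definition the strategy could well give fewer false positives. This stands as a limit on the wording, but the gain would come from volume and growth, which is where the Discussion itself places it.

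**Informal use of a negative result.** The team meeting for nodules above 500 mm³ might weigh a negative CTC. No rule says so. A definition requiring both tests to be positive could raise specificity, but none is stated.

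**The analysis plan is not at hand.** A reader might infer that the absence of a paired test is itself an error. It is not, since an article may leave this to the full protocol or analysis plan. What stands is what the article does fix: estimators for CTC alone, with LDCT as the reference.

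**The named tests.** A reader might also infer that "Chi2 test or Fischer test for qualitative parameters" is the wrong method for two tests on the same patients. The article names those tests for comparing different groups of patients, where they are appropriate, and nowhere proposes them for CTC against LDCT.

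**The data are not the limit.** How often cancer-free patients with nodules are CTC-negative can be estimated from the study, and would inform a different future rule. Only the effect of the present rule on work-ups is settled in advance.

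**Standing of the claim.** It is an expectation in the Discussion, not an objective, hypothesis or sample-size input. That is fair and limits the weight of the first half of the point.

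**Conclusion.** The point holds in this form. Under Table 2, and against LDCT alone with the volume and growth criteria, false-positive work-ups cannot fall; they stay equal only if CTC has no false positives. The direction follows from the rule alone. It rests on taking the CTC-absent column as LDCT alone, which the article supports but does not state. In the 50–500 mm³ category the escalation replaces the three-month growth check with an evaluation, and does not add a work-up where nothing was planned.

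The size is not known. A reader might infer that false positives roughly double. With LDCT false-positive rate f and CTC specificity s, assumed independent, f + (1 − f)(1 − s) does give about double when 1 − s is set equal to f. But f = 10% with s = 99% gives 10.9%, and f = 2% with s = 90% gives 11.8%, so the rise runs from slight to about sixfold. The article supplies neither figure.

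The second half also holds: the estimators as stated give neither the accuracy of the couple, which is the primary objective, nor the contribution of CTC. The change is worth making, and it leaves the enrolment figure untouched.

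**What to change.** 1. Withdraw or restate the Discussion's expectation on false positives so that it agrees with Management of incidental findings and Table 2. The two must be reconciled; no change to the clinical rule is proposed here.
2. Pre-specify a within-patient comparison of the couple (positive if either test triggers work-up) with LDCT alone.
3. Judge both against final cancer status from work-up and follow-up, not against LDCT.
4. Report the differences in true-positive fraction among cancers and in false-positive fraction among cancer-free participants, with paired confidence intervals, and the extra cancers found per extra false-positive work-up.
5. For CTC-positive 50–500 mm³ nodules without a three-month LDCT, the result of LDCT alone is unknown. Give the analysis with these classed as LDCT-positive, then as LDCT-negative.

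**Cost.** Both tests and at least three years of follow-up are already planned, so no new procedure is needed. The work is to define final cancer status and to carry the two-way bound. The sensitivity contrast will be imprecise: with about 30 cancers, power for a 10-point gain is about 7%. Estimates and intervals should therefore carry the conclusion.

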## Data Availability

Not applicable.

## Abbreviations

AAA: Abdominal aortic aneurysm
CT: Computed tomography
CTC: Circulating tumor cells
ECOG: Eastern cooperative oncology group
EDTA: Ethylene-diamine-tetraacetic acid
ISET: Isolation by size of epithelial tumor cells
LDCT: Low-dose chest CT
PAD: Peripheral arterial disease
PET/CT: Positron emission tomography–computed tomography
